### Study population

The study will enrol patients with paroxysmal or persistent AF referred for their first catheter ablation. Detailed inclusion and exclusion criteria are displayed in Table 1.

**Table 1 Tab1:** Inclusion and exclusion criteria

Inclusion criteria	Exclusion criteria
Age: 18–75 years Paroxysmal or persistent (shorter than 1 year) AF Referral for first catheter ablation At least one of the following risk factors: BMI ≥ 27 kg/m^2^ LDL-cholesterol > 2.6 mmol/L or total cholesterol > 5.0 mmol/L Hypertension (blood pressure > 130/90 mmHg) Diabetes mellitus with HbA1c ≥ 53 mmol/mol Active smoking Alcohol use > 14 equivalent units of alcohol/week Informed consent	Long-standing persistent AF (persistent for more than 1 year) Permanent AF Asymptomatic AF Prior catheter ablation Paroxysmal AF consisting of one episode with a reversible cause (e.g., fever, surgery, thyroid crisis, ischemic) Severe valvular heart disease Prior or soon foreseen implantation of cardiac device, such as pacemaker or internal cardioverter defibrillator Acute coronary syndrome < 3 months before inclusion Unstable heart failure NYHA class IV, or heart failure necessitating admission < 3 months before inclusion Cardiac surgery < 3 months before inclusion or planned cardiac surgery Malignancy Life expectancy < 1 year Pregnancy

*AF* atrial fibrillation, *BMI* body mass index, *LDL* low-density lipoprotein, *HbA1c* glycohemoglobin, *NYHA* New York Heart Association

The study will be conducted in accordance with the declaration of Helsinki, the good clinical practice, and the applicable regulatory requirements [29]. The locally appointed medical ethics committee has approved the research protocol. All participants will be informed by the investigator and are required to give their written informed consent prior to enrolment.

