### Post-ablation care

Patients of either treatment group will visit the outpatient clinic at 3 months after ablation. At this point, the treating physician will stop any current antiarrhythmic medication. If the patient does not experience any symptoms after ablation, no additional rhythm assessment will be performed, since this will not have therapeutical consequences. In symptomatic patients, arrhythmias will be objectivated with electrocardiogram or multiple holter assessments. If an arrhythmia is confirmed on electrocardiogram or holter after 3 months after the index ablation, patients are offered to recontinue antiarrhythmic medication and to undergo a repeat ablation. Furthermore, patients suffering from persistent AF will undergo cardioversion.

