### Data collection

Assessment of clinical endpoints will take place at hospital visits during the intake, pre-ablation and the follow-up consultations at 3 and 12 months after ablation. Quality of life data will be collected using digital questionnaires at intake, pre-ablation, 3 months after ablation and 12 months after ablation.

An overview of the study procedures is displayed in Table 3.

**Table 3 Tab3:** Study procedures

Study procedure	Intake	Pre-ablation (only in interventional group)	3 months after ablation	12 months after ablation
Assessment of clinical history and clinical endpoints	x	x	x	x
Physical examination including blood pressure and weight	x	x		x
12-lead ECG	x		x	
Laboratory test	x	x		x
Quality of life using EuroQol-5D, AFEQT, Treatment Burden Questionnaire	x	x	x	x

*ECG* electrocardiogram

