### Statistical analyses

Descriptive statistics will be used to report baseline characteristics of the study population. The primary and secondary endpoints can occur during the entire participation period, which is from baseline to ablation (in the intervention group during the risk treatment; in the control group when patients await the ablation) and in 12 months after the ablation. The different pre-ablation durations amongst patients lead to different study participation periods. Therefore, the number of events will be normalized using the participation period and will be reported in numbers per year (the event rate). The clinical hypothesis that the intervention group will have a lower event rate will be tested by fitting a Poisson regression model to the event data and testing the effect of the intervention group using a Wald test. Results will be reported in terms of incidence risk ratios with accompanying 95% confidence intervals. The primary analysis will be on an intention-to-treat basis. Subgroup analyses will be performed on the primary endpoint. Covariates of interest in this study include gender, age, type of AF (paroxysmal vs. persistent) and number and extent of the respective modifiable risk factors as defined in Table 2.

The secondary endpoints will be analysed by means of chi-squared test or Fisher’s exact test depending on the number of occurrences. Changes in weight and blood pressure will be compared using the appropriate test (unpaired *t* test or Mann–Whitney *U* test), depending on the distribution of data. Laboratory tests will be analysed for differences by fitting linear mixed models to the data.

A cost-effectiveness analysis will be included, covering incremental cost-effectiveness ratio (ICER) and an evaluation of change in patient value, using the EuroQol-5D and AFEQT questionnaires and healthcare-related costs of intervention. Differences in medical hospital costs for both study groups will be compared using the appropriate statistical test (unpaired *t* test or Mann–Whitney *U* test), depending on the distribution of data. Cost savings associated with the study intervention will be calculated by subtracting the cost of the intensive treatment from the cost of the conventional treatment. The completed EuroQol-5D, AFEQT and TBQ questionnaires will be analysed for differences between treatment groups at different moments by fitting linear mixed models to the data.

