### Sample size

The number of hospital admissions in the control group is estimated as 1.0 per patient per year [33, 34]. The proposed intervention is expected to reduce the primary endpoint with 30%. Taking the pre-ablation period into account, in the intervention group, we expect an overall event rate of 0.75 per patient per year. Assuming a balanced design with equal allocation of patients to the two groups, the minimum sample size to achieve an 80% power with 5% Type I error on the primary analysis is 144 (72 per treatment group). A total of 150 patients will be enrolled in this study, taking dropouts into account.

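### The primary Poisson test leaves the role of AF type open and names no allowance for extra-Poisson variation; one sentence fixing both would be a free improvement

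*Protocol article*

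**What the plan says.** All the relevant text is in the Protocol article.

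- **Primary test** (Statistical analyses): "fitting a Poisson regression model to the event data and testing the effect of the intervention group using a Wald test". The sentence names the group effect as what is tested. It does not say what else the model contains, or how the standard error is obtained.
- **Exposure** (same section): "the number of events will be normalized using the participation period and will be reported in numbers per year". This is consistent with a log-time offset, though the word is not used.
- **AF type** (same section): "Subgroup analyses will be performed on the primary endpoint", followed at once by "Covariates of interest in this study include gender, age, type of AF (paroxysmal vs. persistent" and the modifiable risk factors. Whether this list defines subgroups, model covariates or both is not stated.
- **Known at entry** (Study population, Table 1): eligibility requires "Paroxysmal or persistent (shorter than 1 year) AF". Table 3 (Data collection) has an intake column for "Assessment of clinical history and clinical endpoints".
- **Link to the endpoint** (Post-ablation care): "patients suffering from persistent AF will undergo cardioversion". Cardioversion is one of the two components of the primary endpoint (Endpoints).
- **Planned size** (Sample size): a control rate of 1.0 per patient-year, and for the intervention group "we expect an overall event rate of 0.75 per patient per year". The minimum is 144 patients for 80% power at 5% type I error, with 150 to be enrolled.

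**The concern.** Two separate things are left open.

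The first is precision. If AF type predicts re-ablation and cardioversion, a model without it leaves explainable variation in the treatment comparison. The variable is collected anyway.

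The second is the error rate. A Poisson model sets the variance of a patient's count equal to its mean. If patients differ in their underlying rates, counts vary more than that, the default standard error is too small, and a true null is rejected more than 5% of the time. AF type is one source of such variation. Another is clustering: under Post-ablation care, one confirmed arrhythmia can lead to both a repeat ablation and a cardioversion.

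Leaving the covariates' role open also permits a choice between models after the data are seen.

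**Working it through.** **1. The plan's own figure.** The two-sample Wald formula on the log rate ratio is n per arm = (1.96 + 0.842)² × (1/1.0 + 1/0.75) / (t × ln(0.75)²). It gives 222, 178 and 148 per arm for t = 1.0, 1.25 and 1.5 years. The stated 72 per arm is not reproduced. That is a separate matter, needed here only as context for power.

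**2. Inputs.** From the article: 150 patients (75 per arm), rates 1.0 and 0.75 per year, 12 months of follow-up after ablation, and at most 6 months before it in the intervention group. Assumed, not in the article: persistent share p = 0.4; participation T = 1.25 years; persistent-to-paroxysmal rate ratio k = 1.5, 2 or 3; a gamma-distributed multiplicative residual with variance v = 0 or 0.3; two-sided 5% test.

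**3. Analytic check of the group-only test with default errors.** The squared coefficient of variation of the rate due to AF type is c = p(1−p)(k−1)² / (1+(k−1)p)².

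- k = 1.5: 0.24 × 0.25 / 1.2² = 0.042
- k = 2: 0.24 × 1 / 1.4² = 0.122
- k = 3: 0.24 × 4 / 1.8² = 0.296

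Overdispersion is D = 1 + T × [(1+c)(1+v) − 1], with mean control rate 1.0. Type I error is 2(1 − Φ(1.96/√D)).

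- v = 0: D = 1.05 / 1.15 / 1.37, type I error 5.6 / 6.8 / 9.4%
- v = 0.3: D = 1.44 / 1.57 / 1.86, type I error 10.3 / 11.8 / 15.0%

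For p from 0.25 to 0.5 and T from 1.0 to 1.5, with v = 0, the ranges are 5.4-5.7%, 6.3-7.2% and 8.0-11.0%.

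**4. Simulated type I error** (60,000 null trials per setting; k = 1.5 / 2 / 3):

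| Model and standard error | v = 0 | v = 0.3 |
|---|---|---|
| Group only, default | 5.6 / 6.7 / 9.3% | 10.2 / 11.6 / 15.1% |
| Group only, robust | 5.1 / 5.2 / 5.2% | about 5% (4.8-5.5% over all settings, 10,000-trial check) |
| Group + AF type, default | 5.0 / 4.8 / 5.0% | 9.5 / 9.8 / 10.7% |
| Group + AF type, robust | 5.2 / 5.1 / 5.2% | 5.2 / 5.4 / 5.4% |

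A fresh run of 40,000 trials per setting for this write-up agreed within simulation error. With unequal participation (1.5 against 1.25 years, with offset, v = 0), group only with default errors gives 5.5 / 6.8 / 9.7% and AF type with robust errors gives 5.2 / 5.0 / 5.2%.

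**5. What AF type itself adds.** The standard deviation of the log rate ratio under the null falls as follows.

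- v = 0: from 0.151 / 0.158 / 0.173 to 0.148 in each case, a cut of about 2 / 7 / 14%
- v = 0.3: from 0.177 / 0.185 / 0.202 to 0.175 / 0.177 / 0.181, a cut of about 1.5 / 5 / 10%

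Power at 0.75 against 1.0, with robust errors in both models (30,000 trials):

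- v = 0: 43.3 / 40.7 / 36.1% group only, 44.7 / 44.7 / 44.9% with AF type; gain 1.4 / 4.0 / 8.8 points
- v = 0.3: 34.7 / 32.9 / 29.0% group only, 35.6 / 35.6 / 34.0% with AF type; gain 0.9 / 2.7 / 5.0 points

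Comparing the two models with default errors shows almost no gain. That comparison flatters the group-only test, whose rejection rate is already inflated.

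**The case against.** The strongest reply is that nothing stated is wrong. This is a condensed article; exact model terms and the type of standard error are commonly left to the full protocol or SAP, which are not shown. An unadjusted primary analysis is legitimate in a 1:1 randomised trial, and no stratification by AF type is mentioned that would call for adjustment. All of that stands, and it is why the point is an improvement and not an error.

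Three stronger readings are tempting and should be resisted.

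- A reader might infer that the primary model holds the group term only. The text says which effect is tested, not that other terms are excluded, and it lists AF type in the same paragraph. The role is open, not settled as absent.
- A reader might infer that leaving out AF type causes the inflated error rate. Robust errors hold it near 5% without AF type. AF type with default errors leaves 9.5-10.7% when residual variance is 0.3.
- A reader might infer that the trial's test will be anticonservative by the amounts shown. The article does not say that default errors will be used. It gives no persistent share, no AF-type rate ratio and no between-patient variance. The cardioversion sentence concerns care after ablation, so it makes baseline AF type plausibly prognostic without showing by how much. The simulation also treats counts within a patient as uncapped Poisson, which the article neither supports nor rules out.

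Choosing AF type from the list is a judgement. The case for it is its link to a component of the primary endpoint.

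**Conclusion.** The point holds as a free improvement. The section names no model term beyond group, makes no provision for extra-Poisson variation, and does not fix what AF type is for. The intention-to-treat comparison is valid and unbiased either way.

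The size is conditional on 40% persistent AF, 1.25 years and an AF-type rate ratio of 1.5 to 3. A group-only test with default errors would then run at about 5.5-9.5% type I error with no other variation, and at 10-15% with residual variance 0.3. Robust errors do the work of restoring about 5%. AF type adds modest precision: negligible at a ratio of 1.5, about 4 power points at 2 and 8 to 9 at 3, and less if residual variation is present. If AF type is not prognostic and rates do not otherwise vary, neither change matters.

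Even with both changes, power at the planned rates is about 45% under these assumptions, so the sample-size shortfall remains a separate issue.

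**What to change.** In Statistical analyses, state that the primary Poisson model contains treatment group and AF type at randomisation (paroxysmal or persistent) as a prespecified covariate, with log participation time as offset and robust (sandwich) standard errors, and that the Wald test is on the group term. Give the subgroup analyses and their factors a sentence of their own.

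The cost is a change of wording. It needs no new data and no extra patients. It adds one model term against about 164 expected events: 75 × 1.25 × (1.0 + 0.75). Robust errors cost no power when there is no overdispersion (44.7% against 44.6% at a rate ratio of 2, with AF type in the model). If the full protocol or SAP already says this, the only action is to bring the article's sentence into line.

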### Lifestyle interventions

Patients in the lifestyle intervention group will undergo an elaborate risk factor assessment at the nurse-led outpatient clinic. This assessment involves measuring body weight and length, blood pressure, a blood test for cholesterol and diabetes, and a home sleep apnoea test (HSAT). The HSAT is performed with a WatchPAT™ 300, which has previously been validated in a cohort of AF patients [30]. Furthermore, lifestyle behaviour such as physical inactivity, alcohol consumption and smoking are assessed in a structural interview. The risk factor definitions and treatment targets are presented in Table 2. If there are too many risk factors to be treated in a reasonable way for the patient (e.g., it would take too much time and effort), the physician will decide which risk factors will be treated, together with the patient in a shared-decision making approach. During the lifestyle intervention, patients will have approximately 3–5 physical appointments with the nurse–practitioner as well as a 10-min consultation with the cardiologist. Further additional consultations for risk interventions will take place as described in Table 2. The ablation will be scheduled when treatment targets are reached, or, if targets are not reached, at maximally 6 months after study enrolment.

**Table 2 Tab2:** Risk factor interventions and targets in the lifestyle intervention group

Risk factor definition	Target and intervention
Overweight: BMI ≥ 27 kg/m^2^	10% body weight reduction is targeted. Treatment consists of additional consultations with a dietician and a physical fitness and activity programme
Physical inactivity: less than 3,5 h of merely vigorous physical activity per week and limitations during activity	> 3.5 h of physical activity per week is targeted. This is supported by a physical fitness and activity programme guided by a physiotherapist or sport cardiologist
Excessive alcohol consumption: > 8 units a week for women and > 14 units a week for men	We aim for a reduction to ≤ 8 units a week for women and ≤ 14 units a week for men. This is supported by behaviour counselling
Tobacco consumption	Patients should quit smoking. A smoking cessation programme is conducted over 6 weeks by a certified nurse
Hypertension: > 130/90 mmHg	Target blood pressure is < 130/90 mmHg. The lifestyle interventions above and antihypertensive medication are used

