### Usual care

In the usual care group, patients will visit the cardiologist and receive standard treatment according to current guidelines. The cardiologist verifies the patient’s eligibility for ablation and may start additional interventions, such as hypertension management and refer high-risk patients for OSA diagnosis and treatment.

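### The risk-factor count planned for analyses of the primary endpoint includes sleep apnoea, which is tested systematically only in the intervention arm, so equal counts do not mean comparable patients in the two arms

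*Protocol article*

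**What the plan says.** The Statistical analyses section states that "Subgroup analyses will be performed on the primary endpoint". The next sentence gives the covariates of interest: gender, age, type of AF, and the "number and extent of the respective modifiable risk factors as defined in Table 2".

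Table 2 is headed "Risk factor interventions and targets in the lifestyle intervention group" and has eight rows. Six correspond to the eligibility factors in Table 1: BMI, cholesterol, blood pressure, diabetes, smoking and alcohol. The other two are:

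- **OSA**, suspected at an apnoea–hypopnoea index of 5 or more per hour on the home sleep test.
- **Inactivity**, given as "Physical inactivity: less than 3,5 h of merely vigorous physical activity per week and limitations during activity".

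On who is assessed, the Lifestyle interventions section says: "Patients in the lifestyle intervention group will undergo an elaborate risk factor assessment at the nurse-led outpatient clinic". That assessment contains the sleep test, and in it "lifestyle behaviour such as physical inactivity, alcohol consumption and smoking are assessed in a structural interview". Under Usual care, the cardiologist may "refer high-risk patients for OSA diagnosis and treatment". The Background adds that OSA screening lies outside the standard work-up and is considered only on high suspicion.

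**The concern.** Randomisation protects a subgroup comparison only if subgroup membership is determined in the same way in both arms. Here one component of the count is produced by the intervention itself: everyone in that arm is tested for OSA, while controls are investigated on suspicion. A control with two recorded factors may have a third that nobody looked for. An intervention patient with two recorded factors has been tested for it.

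The Background describes OSA as harmful to AF treatment results, so the unrecorded factor is expected to raise the event rate. At the same recorded count, controls would then have a worse prognosis, and the comparison would favour the intervention through classification alone (stage migration). Entering the count as an adjustment covariate distorts the treatment estimate in the same direction. An OSA subgroup would set all test-positive intervention patients against the few controls selected for referral.

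**Working it through.** **Where each Table 2 factor is ascertained**

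| Factor | Intervention arm | Usual care arm |
|---|---|---|
| BMI, cholesterol, blood pressure, diabetes, smoking, alcohol | Eligibility (Table 1) and clinic assessment | Eligibility (Table 1) |
| OSA | Home sleep test for all | Optional referral of high-risk patients |
| Inactivity | Structured interview | Not stated; intake history (Table 3) might record it |

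The protocol gives no figure for this point, so the size can only be illustrated.

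**Assumptions (none from the documents).** Six shared factors at 35% each; OSA and inactivity at 50% each; all independent; at least one shared factor (eligibility); identical populations in both arms.

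**Step 1: share with three or more recorded factors.** Binomial(6, 0.35) gives P(0) = 0.0754, P(1) = 0.2437, P(2) = 0.3280, P(≥3) = 0.3529. Dividing by 1 − 0.0754 = 0.9246 gives 0.2635, 0.3548 and 0.3817 for one, two and three or more shared factors.

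- Intervention, both extra factors recorded: 0.3817 + 0.3548 × 0.75 + 0.2635 × 0.25 = 0.714, or 71%.
- Control, neither recorded (worst case): 0.382, or 38%.
- Control, inactivity recorded but no OSA: 0.3817 + 0.3548 × 0.5 = 0.559, or 56%.
- Control, inactivity recorded and half of OSA detected: 0.3817 + 0.3548 × 0.625 + 0.2635 × 0.125 = 0.636, or 64%.

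**Step 2: rate ratios with no treatment effect.** Assume that the event rate rises 1.25-fold per true factor. An unrecorded factor at 50% then multiplies the mean rate by 1 + 0.5 × 0.25 = 1.125.

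Fewer than three recorded factors:

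- Intervention: (0.0659 × 1.25 + 0.1318 × 1.5625 + 0.0887 × 1.5625) / 0.2863 = 1.491.
- Control, worst case: (0.2635 × 1.25 + 0.3548 × 1.5625) / 0.6183 × 1.125² = 1.809. Ratio 1.491/1.809 = **0.82**.
- Control, only OSA unrecorded: (0.1318 × 1.25 + 0.1318 × 1.5625 + 0.1774 × 1.5625) / 0.4409 × 1.125 = 1.653. Ratio 1.491/1.653 = **0.90**.

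Three or more recorded factors. The overall mean is the same in both arms: (1.0875⁶ − 0.0754) / 0.9246 × 1.125² = 2.161.

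- Intervention: (2.161 − 0.2863 × 1.491) / 0.7137 = 2.430.
- Control, worst case: (2.161 − 0.6183 × 1.809) / 0.3817 = 2.73. Ratio **0.89**.
- Control, only OSA unrecorded: (2.161 − 0.4409 × 1.653) / 0.5591 = 2.56. Ratio **0.95**.

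The overall ratio is 2.161/2.161 = 1.00, so the unadjusted comparison is untouched. With a weaker gradient of 1.10 per factor, the worst-case ratios are 0.92 and 0.95.

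**Step 3: other assumptions.** Shared factors at 50/50/50/10/15/15%, OSA at 30–70%, inactivity at 30–60%, 0–50% of control OSA detected, control inactivity not recorded, gradient 1.25. The share with three or more factors is 53–77% in the intervention arm against 30–44% in control. The null rate ratios are 0.78–0.91 below three factors and 0.85–0.95 at three or more.

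**The case against.** - **Inactivity may be recorded in both arms.** This stands. The interview is described only for the intervention arm, but it also covers smoking and alcohol, which are known for controls. Clinical history is taken from everyone at intake, and a condensed article need not list its contents. Inactivity is a probable second problem, and OSA carries the point.
- **Controls can be diagnosed with OSA.** True, so it would be wrong to say that OSA is found only in the intervention arm. Universal testing against referral on suspicion is still two rules.
- **Table 3 shows no sleep test for controls.** A reader might cite this, but Table 3 lists none for the intervention arm either. Its silence proves nothing; the case rests on the Lifestyle interventions and Usual care sections.
- **Coding belongs in the analysis plan.** Often so, but the article itself ties the variable to Table 2 and places the sleep test in one arm.
- **Missing data will be imputed.** Control sleep-test results are absent by design, so imputed values would come almost entirely from the intervention arm.
- **The covariates may not be subgroup variables.** Their position straight after the subgroup sentence suggests that they are. If they are adjustment terms instead, the same distortion enters the adjusted estimate.

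**Conclusion.** The point holds for OSA and probably for inactivity. Following the text as written, the two arms would be classified by different rules after randomisation, and comparisons at a given risk-factor count would lean towards the intervention. The 71% against 38% split is a worst case on assumed prevalences, and it narrows to 71% against 56% or 64% as more is recorded in controls. The spurious rate ratios likewise depend on the assumed gradient and prevalences.

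Two stronger readings are not supported:

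- A reader might infer spurious effect modification by risk-factor load. In the worst case both strata shift in the same direction, and the ratio between them is only 0.95/0.92 = 1.03 to 0.89/0.82 = 1.08. That is too small to show as an interaction with 150 patients. The distortion is within strata.
- A reader might infer that the primary result is biased. The stated primary test is a Wald test of group in a Poisson model by intention to treat, with no stated adjustment for the count, so it is unaffected.

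**What to change.** Replace the reference to Table 2 with one sentence: risk-factor count, subgroups and covariates use only factors measured in the same way at intake in both arms, namely the Table 1 items (BMI, cholesterol, blood pressure, HbA1c, smoking, alcohol).

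- State one alcohol cut-off for this analysis. Table 1 uses more than 14 units a week for everyone and Table 2 more than 8 for women, so the two must be reconciled. The diabetes entries of the two tables also differ in wording, so the definition used should be named.
- Include inactivity only if it is recorded identically at intake in both arms.
- Report OSA findings descriptively in the intervention arm.

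The cost is the between-arm OSA subgroup comparison, which is not valid as planned. The primary analysis does not change.

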### Endpoints

The primary composite endpoint of the study is the number of hospitalizations for re-ablation and cardioversion from baseline to 12 months after ablation. The conditions for performing a re-ablation and cardioversion are explained above.

Secondary endpoints are the number of hospitalizations for re-ablation, the number of cardioversions, the number of cancelled ablations because of overall symptom reduction, mortality, number of strokes, acute ischemic events, or hospitalizations for heart failure at 12 months after ablation.

Further secondary endpoints include change in weight, blood pressure and laboratory tests at baseline, after the lifestyle intervention (for the intervention group) and at 1 year after ablation. Furthermore, ablation success is determined at 12 months after ablation. The ablation is considered to be successful when patients can stop their antiarrhythmic drugs after 3 months, without having recurrence of symptomatic arrhythmias urging for re-ablation. The elaborate lifestyle changes might negatively affect treatment burden. Treatment burden is the perception of cumulative work a patient has to perform to manage their health, and should, therefore, be limited. Therefore, further secondary endpoints include the change in quality of life and treatment burden from baseline to before ablation, at 3 months, and 12 months after ablation. The patient’s general quality of life will be assessed with the Dutch version of the EuroQol-5D questionnaire. This questionnaire includes 5 health-state measures and is suitable to determine quality-adjusted life-years for a cost–utility analysis [31]. AF-specific quality of life is assessed with the Dutch version of the AF effect on Quality of Life Survey (AFEQT). This questionnaire is suitable for describing AF-related symptoms [32]. Treatment burden will be evaluated with a Dutch translation of the Treatment Burden Questionnaire.

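### Cardioversions and other secondary events that accrue over time are assigned chi-squared or Fisher tests, although the same section says unequal participation calls for rates

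*Protocol article*

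**What the plan says.** All references are to the protocol article.

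- **Endpoints** words the event-type secondary endpoints as counts: "Secondary endpoints are the number of hospitalizations for re-ablation, the number of cardioversions, the number of cancelled ablations because of overall symptom reduction". Mortality and "number of strokes, acute ischemic events, or hospitalizations for heart failure at 12 months after ablation" follow in the same sentence. Ablation success at 12 months is a further secondary endpoint.
- **Statistical analyses, first paragraph**, sets the window: "The primary and secondary endpoints can occur during the entire participation period", which it defines as baseline to ablation plus the 12 months after it. It adds that "The different pre-ablation durations amongst patients lead to different study participation periods". It draws the consequence that "the number of events will be normalized using the participation period and will be reported in numbers per year (the event rate"), and tests the clinical hypothesis by "fitting a Poisson regression model to the event data and testing the effect of the intervention group using a Wald test".
- **Statistical analyses, second paragraph**, then says: "The secondary endpoints will be analysed by means of chi-squared test" or Fisher's exact test, depending on the number of occurrences. Weight, blood pressure, laboratory values and questionnaires get their own methods, so this sentence governs the event-type secondary endpoints.

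**The concern.** The first paragraph names secondary endpoints explicitly, identifies unequal exposure as a problem for them, and gives the remedy. The second paragraph assigns those endpoints to tests that cannot apply the remedy. A chi-squared or Fisher test compares proportions of patients and has no place for time at risk.

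Two consequences follow.

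- **Exposure.** If one arm is observed for longer, more of its patients have an event even when the true rates are equal. The intervention arm may wait up to 6 months for ablation (Lifestyle interventions). The control arm's wait is not stated.
- **Repeat events.** A chi-squared test on independent patients needs one yes/no value per patient. Tabulating raw event counts would break independence. Second and later events therefore drop out, although the primary endpoint counts them.

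Cardioversions, a component of the primary endpoint, can occur before ablation and can recur, so both consequences apply in full.

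**Working it through.** **Plan's own figure.** The article gives no rate, power or error figure for the secondary endpoints, so there is none to reproduce.

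**Inputs from the article.** 150 patients randomised 1:1, so 75 per arm (72 per arm in the power calculation). Ablation in the intervention arm at most 6 months after enrolment, so participation of at most 6 + 12 = 18 months. Rates of 1.0 and 0.75 per patient per year for the primary endpoint (Sample size).

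**Assumptions.** Mean participation in each arm, and secondary event rates (0.05, 0.3 and 0.5 per year). Neither is given, so ranges are shown.

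**Step 1: false positives at equal true rates.** The proportion with any event is p = 1 - exp(-rate x T), with T in years. For example, at 0.3 per year, 18 months gives 1 - exp(-0.45) = 36.2% and 15 months gives 1 - exp(-0.375) = 31.3%. The rejection probability is the exact binomial probability, with n = 75 per arm, that the difference in proportions divided by sqrt(2 p(1-p)/n), with p pooled, exceeds 1.96 in absolute value.

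| Intervention v control (months) | 0.05/year | 0.3/year | 0.5/year |
|---|---|---|---|
| 15 v 15 | 6.1% v 6.1%: rejects 5.1% | 31.3% v 31.3%: 4.9% | 46.5% v 46.5%: 5.6% |
| 16.5 v 15 | 6.6% v 6.1%: 5.4% | 33.8% v 31.3%: 6.1% | 49.7% v 46.5%: 7.5% |
| 18 v 15 | 7.2% v 6.1%: 6.1% | 36.2% v 31.3%: 9.7% | 52.8% v 46.5%: 12.9% |
| 18 v 14.4 | 7.2% v 5.8%: 6.6% | 36.2% v 30.2%: 12.0% | 52.8% v 45.1%: 16.5% |
| 18 v 12 | 7.2% v 4.9%: 9.2% | 36.2% v 25.9%: 27.2% | 52.8% v 39.3%: 39.7% |

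The spurious excess falls on the arm observed for longer. At 0.05 per year Fisher's test, computed the same way, rejects 2.7% of the time at 18 v 14.4 months.

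**Step 2: repeat events lost.** If events follow a Poisson process, the share of events that are not a patient's first is 1 - p/(rate x T). At the primary endpoint's 1.0 per year this is 1 - 0.632/1.0 = 37% over 12 months and 1 - 0.777/1.5 = 48% over 18 months. At 0.3 and 0.5 per year over 15 months it is 1 - 0.313/0.375 = 17% and 1 - 0.465/0.625 = 26%.

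**Step 3: a real benefit can be hidden.** Take rates of 1.0 v 0.75 and 72 per arm. These are the composite's rates; a single component will be lower. Poisson Wald power is the normal probability of |ln 0.75| / sqrt[(1/(1.0 x T0) + 1/(0.75 x T1))/72] - 1.96.

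- 12 months in both arms: 36% by Poisson, 24% by chi-squared. This is the cost of dichotomising alone.
- Control 15, intervention 18 months: 47% by Poisson, 7% by chi-squared, since the proportions become 71.3% v 67.5%.

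**Step 4: re-ablation is different.** It can only follow the index ablation, and Post-ablation care offers it for arrhythmia confirmed more than 3 months afterwards. Follow-up is 12 months after ablation in both arms, so a longer wait adds no time at risk. An offset running from baseline would itself mislead: with equal post-ablation risk and 18 v 14.4 months, the rate ratio would be 14.4/18 = 0.80, a spurious 20% benefit.

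**The case against.** Several objections have force.

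- **A reader might infer that every secondary endpoint suffers from unequal exposure.** The article does not support that. Re-ablation has about the same risk window in both arms. Cancelled ablation and ablation success are once-per-patient outcomes for which chi-squared or Fisher is suitable. Death cannot recur, so only the exposure point applies to it.
- **A reader might infer a large false-positive problem.** Eighteen months is the cap in the intervention arm, because ablation is scheduled once targets are reached. With similar waits there is no exposure bias, and if controls wait longer the bias reverses.
- **A reader might infer that the safety comparison is unreliable.** At 0.05 per year the inflation is small: the proportions at 18 v 14.4 months, 7.2% v 5.8%, differ by about one patient in 75. Fisher's test, which the plan allows when occurrences are few, stays below 5% there.
- **A reader might infer that the components cannot be related to the primary result.** That goes too far. The normalisation sentence may mean that component rates per year are reported whatever test is used.
- **No yes/no rule is stated,** and an article may leave that detail to the analysis plan.

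These points narrow the finding but do not remove it. The article does not leave the test open: it names one that conflicts with the reasoning in its preceding paragraph. The phrase placing secondary events at 12 months after ablation does not restrict the window, because Statistical analyses counts them from baseline.

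**Conclusion.** The inconsistency is real and lies within one section. It matters most for cardioversions, where the named tests ignore exposure and, by inference, lose repeat events. For stroke, ischaemic events, heart-failure admission and death, the exposure point stands with little inflation: about 5-9% by chi-squared at 0.05 per year over the durations tried. For re-ablation only the loss of repeats applies.

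For events at 0.3 to 0.5 per year, the chi-squared false-positive rate runs from about 5% with equal participation to 27-40% at 18 v 12 months. Where the trial falls in that range depends on the control wait and the event rates, which the article does not give, so no single figure should be quoted as the size of the bias. Its direction also depends on which arm in fact waits longer. These are secondary analyses and the primary test is not affected. The correction is worth making because it costs little.

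**What to change.** Replace the single sentence on secondary endpoints with a method for each type.

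- **Cardioversions:** a Poisson-type rate model with log participation time as offset, as for the primary endpoint, preferably with robust standard errors. The article states a plain Poisson model with a Wald test, so robust errors would be an addition.
- **Re-ablations:** counts over the post-ablation period only, with time since the index ablation as offset, not time since baseline. Say how patients with a cancelled ablation enter; Trial design already starts their 12 months at the decision to cancel.
- **Mortality, stroke, ischaemic events, heart-failure admissions:** rates with exposure (exact Poisson if sparse), or time to first event from randomisation.
- **Cancelled ablations and ablation success:** keep chi-squared or Fisher's exact test.

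The cost is wording and a little analysis work. Participation periods are already needed for the primary analysis, so no extra data are required.
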